#### Plans to promote participant retention and complete follow-up {18b}

Not applicable.

#### Data management {19}

Data will be collected by the MK on paper sheets and will be entered to Microsoft Excel software by another blinded team researcher and then also will be random-checked by third team member.

#### Plans for collection, laboratory evaluation, and storage of biological specimens for genetic or molecular analysis in this trial/future use {33}

Blood samples will be collected by investigators, will be labeled with subject ID, and then immediately will be sent to the central laboratory (Alzahra Clinical Research Laboratory, Isfahan) for keeping in − 80 °C freezers. After collecting all specimens, laboratory assessment methods will be executed. Storing of biological specimen will be done only if participants accept the secondary informed consent. No genetic studies are currently planned.

### Statistical methods

#### Statistical methods for primary and secondary outcomes {20a}

Analyzing data will be performed in the SPSS 16 (version) software. Normality will be checked by Kolmogorov-Smirnov test. Qualitative data will be reported as frequencies, normal continuous quantitative as mean (± SD) and median (IQR) for others.

Differences within group will be assessed with paired *t*-test and Wilcoxon rank-sum test.

Between group differences also will be assessed using independent *t*-test and Mann-Whitney *U* test. The significance level will be considered *p* < 0.05.

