#### Outcomes {12}

All assessors in this trial will be blinded to intervention allocation.

Serum CRP and ESR as an inflammatory agent, serum lactate dehydrogenase (LDH) as a marker of cell injury, total oxidative stress (TOS), and total antioxidant capacity (TAC) as an oxidative stress biomarker will be measured as our primary outcomes. Secondary outcomes include evaluating duration of hospitalization (days) and 28-day mortality rate, differences in albumin (Alb), alanine aminotransferase (ALT), aspartate aminotransferase (AST), blood urea nitrogen (BUN), and creatinine in blood. Anthropometric variables such as weight, height, body mass index (BMI), mid arm circumference (MAC), and calf circumference will be appraised at baseline.

Estimation of patient height: Due to the limitations in the ICU, the patients’ height is calculated based on the following formula [22]:
$$ \mathrm{Height}\ \left(\mathrm{cm}\right)=153.492-\left(7.97\times \mathrm{sex}\ \left[\mathrm{sex}:\mathrm{man}=1,\mathrm{woman}=2\right]\right)+\left(0.974\times \mathrm{ulna}\ \mathrm{length}\ \left[\mathrm{in}\ \mathrm{cm}\right]\right) $$

Estimation of patient weight: Due to the limitations in the ICU, the patients’ weight is calculated based on Chumlea I formula [23]:
$$ \mathrm{Men}:\left(\mathrm{MAC}\times 2.31\right)+\left(\mathrm{calf}\ \mathrm{circumference}\times 1.50\right)-50.10 $$$$ \mathrm{Women}:\left(\mathrm{MAC}\times 1.63\right)+\left(\mathrm{calf}\ \mathrm{circumference}\times 1.43\right)-37.46 $$

Blood drawing will be executed at baseline and end of the trial. About 10 ml volume of fasted blood (at 6:00 o’clock before first meal) will be collected and then centrifuged, with the serum separated from the sediment, and preserved at temperature of − 20 °C.

Calf circumference method of measurement: The circumference of the leg muscle is measured so that the patient is in the supine position. The patient’s left knee rises high enough to form a right corner between the thigh and the leg. We place the tape around the leg muscle and move it along the leg muscle to meter the largest circumference without any pressure to the subcutaneous tissue [24].

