### Sample size {14}

The number of samples considering the type I error *α* = 0.05 and the type II error *β* = 0.20 with 80% test power and standardized effect size equal to *Δ* = 30 of the following formula based on to detect the inflammation effect based on changes in CRP (as the main outcome of this study) by l-carnitine supplementation (control group: 99.96 ± 33.16, intervention group: 98.48 ± 37.01) using the findings of Noormandi et al. CRP index (mg/dl) [25]:
$$ n=\frac{2\left[{\left({Z}_{1-\frac{\alpha }{2}}+{Z}_{1-\beta}\right)}^2\times {S}^2\right]}{\varDelta^2}=\frac{2\left[{\left(1.96+0.84\right)}^2\times {(37)}^2\right]}{30^2}=23.85 $$

The required sample size in each group has been equal to 24 people, and with considering the drop out patients, the sample size will be practically 30 patients in every group, which we will consider a total of 60. It seems that this sample size is small; however, several articles which conducted among ICU patients used a small sample size based on a formula like our ones and worked on about 60 patients [26–28].

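### The primary between-group test is in effect left to a normality check on each marker, and it ignores the baseline value; one baseline-adjusted analysis per marker should be fixed in advance

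*Protocol article*

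**What the plan says.** The statistical methods section {20a} states: "Normality will be checked by Kolmogorov-Smirnov test". The next sentence ties the descriptive summary to normality: "normal continuous quantitative as mean (± SD) and median (IQR) for others". For the comparison of arms it says: "Between group differences also will be assessed using independent *t*-test and Mann-Whitney *U* test". The threshold is given once: "The significance level will be considered *p* < 0.05".

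The outcomes section {12} lists CRP, ESR, LDH, TOS and TAC, which "will be measured as our primary outcomes". It also says that blood is drawn at baseline and at the end of the trial, so each marker has a baseline value.

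The sample size section {14} calls CRP the main outcome and assumes "the type I error *α* = 0.05 and the type II error *β* = 0.20 with 80% test power". It takes a "standardized effect size equal to *Δ* = 30" with SD 37. Despite its label, 30 enters the formula as a raw difference between two means (30/37 = 0.81 SD).

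No sentence in {20a} says that the normality result selects the between-group test. Baseline adjustment is not mentioned, and the section does not say whether end values or changes are compared.

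**The concern.** Two things in {20a} deserve attention.

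First, the natural reading is that each marker gets a t-test if it passes the normality check and a Mann-Whitney test if it fails. The quantity compared then depends on that marker's own outcome data: a difference in means in one case, a rank comparison in the other. Five primary markers could be reported on different scales. If CRP fails the check, its primary test is no longer the mean comparison for which the trial was sized. The check is also a weak guide at 24 to 30 patients per arm. Section {20c} adds a practical difficulty: it plans multiple imputation, and a normality test can go different ways in different imputed data sets.

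Second, whichever of the two tests is used, it leaves out the baseline value. In a trial this small, that is where precision is lost.

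**Working it through.** **1. The plan's own figure.** Inputs from {14}: difference 30, SD 37, z-values 1.96 and 0.84.

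n = 2 × (1.96 + 0.84)² × 37² / 30² = 23.85, so 24 per arm. This reproduces. Allowing 20% dropout, 24/0.8 = 30.

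Power at 24 per arm: standard error = 37 × √(2/24) = 10.68; 30/10.68 = 2.809; Φ(2.809 − 1.96) = 80.2%.

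**2. What the pre-test does.** Simulation with 10,000 trials per setting and 24 per arm. Normality was tested in each arm at 5%, and Mann-Whitney was used if either arm failed. The article does not say which form of the Kolmogorov-Smirnov test is meant, so both are shown: corrected for an estimated mean and SD (Lilliefors) and uncorrected. Assumed shapes for the end value are normal with SD 37, and lognormal with log-SD 0.36, 0.6 and 0.8. The mildest lognormal is close to the spread in {14} (37/99, a CV of about 0.37). Assumed effects are 30 units for normal data and ratios of 0.7, 0.6 and 0.5 for the three lognormal settings.

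| Shape | Switch to Mann-Whitney (corrected / uncorrected) | Power: t | Power: Mann-Whitney | Power: two-step (corrected / uncorrected) | t and Mann-Whitney disagree |
|---|---|---|---|---|---|
| Normal | 10% / 0% | 78.0% | 75.5% | 77.8% / 78.0% | 5.5% |
| log-SD 0.36 | 42% / 1% | 90.1% | 90.0% | 90.6% / 90.1% | 4.6% |
| log-SD 0.6 | 77% / 7% | 76.4% | 80.3% | 80.8% / 77.9% | 11.1% |
| log-SD 0.8 | 93% / 22% | 71.9% | 81.8% | 82.0% / 77.9% | 15.6% |

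Against the better of the two tests, the two-step rule loses about 0 points in the corrected form. In the uncorrected form it loses 80.3 − 77.9 = 2.4 and 81.8 − 77.9 = 3.9 points on the two more skewed shapes. Type I error of the two-step rule is 4.6% to 5.5% over all null settings at 24 and 30 per arm.

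With exactly normal data and the corrected form, the chance of a switch is 1 − 0.95² = 9.75% per marker. For at least one of five markers, if independent, it is 1 − 0.95¹⁰ = 40%.

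**3. What ignoring baseline does.** With baseline as covariate and baseline-to-end correlation ρ, the residual variance is multiplied by 1 − ρ². The document gives no ρ, so 0.3 to 0.7 is assumed. Taking 37 as the SD of the end value, power = Φ(2.809/√(1 − ρ²) − 1.96) and n = 23.85 × (1 − ρ²).

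| ρ | 1 − ρ² | Power at 24 per arm | Gain over 80.2% | n per arm for 80% |
|---|---|---|---|---|
| 0.3 | 0.91 | 83.8% | 3.6 points | 22 |
| 0.5 | 0.75 | 90.0% | 9.8 points | 18 |
| 0.7 | 0.51 | 97.6% | 17.4 points | 13 |

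Section {14} speaks of changes in CRP. If 37 were instead the SD of the change, the variance factor would be (1 + ρ)/2, that is 0.65, 0.75 and 0.85. Power would be 93.6%, 90.0% and 86.1%, a gain of 13, 10 and 6 points, which lies within the same range.

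**4. Separating the two effects.** A second simulation used 24 per arm, lognormal end values with a treatment ratio of 69/99, and ρ = 0.5 (assumed).

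| CV | Two-step rule | Fixed log-scale t-test, no baseline | Log-scale model with baseline |
|---|---|---|---|
| 0.37 | 91% | 92% | 97% |
| 0.6 (assumed) | 55–57% | 59% | 70% |
| 0.8 (assumed) | 38–41% | 42% | 51% |

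Replacing the pre-test with a fixed log-scale test gains 1 to 4 points. Adding baseline gains a further 5, 11 and 9 points.

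**The case against.** The strongest reply is that the pre-test is nearly harmless here, and on operating characteristics that is right. A reader might infer that it inflates false positives; the simulated 4.6% to 5.5% does not support that. A reader might also infer that it costs ten or more points of power, by setting the first column of the last table against the third. That comparison changes two things at once, and most of the gap belongs to baseline adjustment.

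Four further points stand:

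- The selection rule is inferred, because the normality sentence leads directly only into how data are summarised. If the inference is rejected, however, the section names two tests per marker with no rule for choosing between them, so the effect measure is still not fixed.
- The form of the Kolmogorov-Smirnov test is detail that an article may leave to a fuller document. It is used above only to show a range.
- The larger disagreement rates, 11% to 16%, come from assumed strong skew. Near the spread given in {14} they are about 5%, and in every setting they are an upper limit on how often the choice of test could change the conclusion.
- Nothing in the document shows that all five markers are skewed, so it gives no ground for logging all of them.

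The simulations model end values. If changes are analysed, the switching rates may not carry over. Blinding of the analysts ({17a}) limits deliberate choice but does not stop the test from depending on the data.

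**Conclusion.** The point holds in a limited form. The effect measure for each primary marker is in effect left to a weak check on the outcome data, and the implied rule can move the analysis away from the mean difference on which the trial was sized. This is a weakness of pre-specification, not a threat to validity: type I error stays near 5% and the power cost is about 0 to 4 points. The larger cost, about 4 to 17 points for the plan's own CRP scenario, comes from comparing the arms without the baseline values. That size rests on assumed correlations of 0.3 to 0.7 and a linear relation between baseline and end value. The pre-test figures rest on assumed distribution shapes.

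**What to change.** In {20a}, drop the normality test as a decision rule and state one between-group analysis for each primary marker: a linear model (ANCOVA) of the end value on group with the baseline value as covariate, reported with a 95% CI. Fix the scale before the data are seen: log for CRP and for any other marker expected on prior grounds to be right-skewed, with baseline logged too, and the original scale otherwise. Check residuals by plots, and keep Mann-Whitney as a sensitivity analysis for all five markers.

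This costs wording only. Baseline samples are already planned, and no extra patients or measurements are needed. The downside is that log-scale results are ratios of geometric means, not differences in the units of the sample size calculation, so the text should say how they relate to the 30-unit target.

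### The plan names the rank-sum test for before-after differences, and its between-arm tests have no baseline covariate and no stated scale, so free precision is not used

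*Protocol article*

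**What the plan says.** Protocol article, Statistical methods for primary and secondary outcomes {20a}: "Differences within group will be assessed with paired" t-test and "Wilcoxon rank-sum test". The next sentence reads "Between group differences also will be assessed using independent" t-test and Mann-Whitney U test, and the threshold is p < 0.05 throughout. The section names no covariate, does not give the analysed quantity (end value or change), and does not say which comparison carries the conclusion.

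Outcomes {12} makes CRP, ESR, LDH, TOS and TAC primary, and adds: "Blood drawing will be executed at baseline and end of the trial". The Abstract records APACHE II and SOFA at baseline.

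Sample size {14} is set "with 80% test power" for CRP as the main outcome. It speaks of changes in CRP, but takes its SD from group summaries in an earlier trial, such as "intervention group: 98.48 ± 37.01".

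**The concern.** There are three linked problems.

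- **Wrong paired test.** The rank-sum test is the Mann-Whitney U test under another name. It treats baseline and end values as coming from different patients and discards the pairing. The paired counterpart is the signed-rank test.
- **Unused baseline.** Neither the independent t-test nor Mann-Whitney U takes a covariate. In a trial of 60, part of the noise in the end value could be removed with data already collected. Because the scale is not fixed, the more favourable of two analyses could also be chosen later.
- **No stated basis for the conclusion.** Within-arm and between-arm tests stand side by side at the same threshold. Both arms receive standard sepsis treatment, so CRP may fall in both whatever the supplement does. Significance in one arm only could then be mistaken for a treatment effect.

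**Working it through.** **Inputs from Sample size {14}:** two-sided alpha 0.05, SD 37, difference 30, 24 evaluable per arm, 30 per arm recruited. The protocol calls the 30 standardized, but its formula uses it in CRP units. **Assumptions:** the baseline-to-end correlation r is not given, so a range is shown; baseline and end SDs are taken as equal; data are taken as normal.

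**1. The plan's own figure.** n = 2(1.96 + 0.84)² × 37² / 30² = 23.85, so 24 per arm. This reproduces. By the normal approximation, 24 per arm gives 80.2% power; by the noncentral t distribution it gives 78.5%. The noncentral t is used below.

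**2. Power if 37 is the SD of a single measurement.**
- End value: SD 37
- Change score: SD = 37√(2(1 − r))
- ANCOVA: SD = 37√(1 − r²)

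| r | SD change | SD ANCOVA | Power, change | Power, end value | Power, ANCOVA |
|---|---|---|---|---|---|
| 0.2 | 46.8 | 36.3 | 59% | 79% | 80% |
| 0.3 | 43.8 | 35.3 | 64% | 79% | 82% |
| 0.5 | 37.0 | 32.0 | 79% | 79% | 89% |
| 0.7 | 28.7 | 26.4 | 94% | 79% | 97% |

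**3. Power if 37 is the SD of change.** The change score then has 79% power at any r. The ANCOVA SD is 37√((1 + r)/2), that is 28.7, 29.8, 32.0 and 34.1 at r = 0.2, 0.3, 0.5 and 0.7. Power is 94%, 93%, 89% and 85%. ANCOVA is the highest in every row under both readings.

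**4. Chance baseline imbalance.** The standard error of the baseline difference is 37√(2/24) = 10.7. An imbalance of that size shifts the expected end-value difference by r × 10.7 and the change-score difference by (r − 1) × 10.7. At r = 0.3 these are +3.2 and −7.5. The two unadjusted analyses are thus pulled in opposite directions. ANCOVA removes the shift.

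**5. Rank-sum on paired data.** Simulation with 30 pairs:

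| r | Type I error, rank-sum | Type I error, signed-rank | Power at 0.5 SD shift, rank-sum | Power, signed-rank |
|---|---|---|---|---|
| 0.3 | 2.0% | 5.0% | 45% | 60% |
| 0.5 | 0.8% | 4.9% | 44% | 74% |
| 0.7 | 0.1% | 4.9% | 43% | 92% |

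**6. Separate within-arm tests.** Simulation with paired t-tests, 24 per arm, no treatment effect and a common fall of 10 to 20 units (r 0.3 to 0.7): only the active arm is significant in about 9% to 25% of trials. With no common fall the figure is about 5%.

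**The case against.** The case for leaving the text alone has four parts.

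- **The baseline may be used.** A reader might infer that the plan ignores baseline values. The document does not establish this. Sample size {14} speaks of changes in CRP, and Outcomes {12} speaks of differences in several secondary blood tests, so a t-test on change scores is possible. This stands. What can be said is that no adjustment is named and the scale is not stated.
- **Within-arm tests may be only descriptive.** A reader might infer that they will serve as evidence of efficacy. Nothing says so: the study design is a placebo-controlled superiority trial and between-arm tests are planned. This stands too. The text merely leaves the role of each comparison open.
- **The unadjusted test is sound.** It is valid under randomisation, and the planned size meets its target by the formula used. At r = 0.3 ANCOVA gains only about 3 points over end values. This is right, so the loss is one of efficiency relative to ANCOVA and not an error. But the gain costs nothing, and a change-score test can fall well short when r is low.
- **Rank-sum is a naming slip.** It is listed with the paired t-test, and Mann-Whitney is named separately, so signed-rank was probably meant. Taken literally the test is conservative, and it does not touch the randomised comparison. That limits the harm, but the text is still wrong as it stands.

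A condensed article may leave the scale and covariates to a fuller document. That excuses missing detail. It does not excuse a test named wrongly.

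**Conclusion.** The point holds in limited form. The rank-sum label is an error in the text, and its effect is confined to within-arm p-values: type I error of about 2% down to 0.1% for r from 0.3 to 0.7. The between-arm tests as named are valid but give up precision. Against end values, ANCOVA gains about 2 to 19 points of power over r from 0.2 to 0.7. Against change scores it gains 3 to 22 points if 37 is the SD of a single measurement, and 6 to 15 points if it is the SD of change. All these sizes rest on an assumed r and on which reading of the SD is right; the protocol settles neither. ANCOVA does best under each reading. The document does not support the stronger claims that baseline is ignored or that within-arm p-values will carry the efficacy conclusion.

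**What to change.** In section {20a}:

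1. Make the primary between-arm analysis an ANCOVA of end-of-treatment CRP (log scale if skewed) on arm and baseline CRP. Report the adjusted difference with its 95% CI. Use the same model for ESR, LDH, TOS, TAC and the other biomarkers measured twice.
2. State that the between-arm comparison alone carries the efficacy conclusion, and present within-arm changes descriptively.
3. If a paired non-parametric test is kept, replace rank-sum with signed-rank.

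Baseline SOFA or APACHE II may be added as one severity covariate; this is optional.

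The cost is wording only. The baseline blood values are already collected, no extra patients or visits are needed, and the model runs in the software named.

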#### Interim analyses {21b}

An independent statistician will carry out an interim analysis (the logistic regression model) for safety and adverse events when we have reached 50% of the events between two groups. Then, the results will be evaluated by the trial steering committee.

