### Assignment of interventions: allocation

#### Sequence generation {16a}

Each patient will be recruited into intervention or control group using a random number generating website: https://www.sealedenvelope.com/simple-randomiser/v1/lists. Eligible patients will be randomly allocated in a ratio of 1:1 to receive l-carnitine or placebo with a block size of four. Allocation sequence will be determined by sequence in permuted blocks of four. A block size of four is constructed 6 different block to assign patients to the trial groups as follows equally:

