#### Adverse event reporting and harms {22}

Although many studies indicated this normal dosage of l-carnitine has no considerable adverse effects, it might have some minor side effects such as diarrhea and fish odor syndrome [21]. Nevertheless, any adverse events that occur during the study will be reported to the Department of Community Nutrition and ethical committee of Isfahan University of Medical Sciences for decision-making.

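### The one named between-arm safety method, logistic regression, gives no usable estimate for an adverse event type seen in only one arm; counts with exact or score intervals would serve better (minor)

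*Protocol article*

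**What the plan says.** Interim analyses {21b} provides: "An independent statistician will carry out an interim analysis (the logistic regression model) for safety and adverse events", to be done "when we have reached 50% of the events between two groups", with the results going to the trial steering committee. The section does not say which test or interval is taken from the model, which events enter it, or whether it is fitted per event type.

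No other between-arm safety comparison is named. Statistical methods {20a} lists frequencies, t-tests and rank tests, with no between-group test for binary data. The only threshold in the article, "The significance level will be considered *p* < 0.05", stands in that section, which covers the primary and secondary outcomes. The sections on discontinuation {11b} and on harms {22} provide for case-by-case handling and reporting.

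On expected harms, {22} says that the dosage "has no considerable adverse effects, it might have some minor side effects such as diarrhea and fish odor syndrome". On size, Sample size {14} says "the sample size will be practically 30 patients in every group, which we will consider a total of 60".

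**The concern.** The side effects named in {22} are attributed to l-carnitine and at least one of them, fish odor, would be unusual on placebo. In arms of 30 or fewer, such an event may well be seen in the active arm only. That pattern deserves the committee's attention, and it is the one that ordinary logistic regression handles worst: the likelihood keeps rising as the log-odds ratio grows, so there is no finite estimate. Software stops at an arbitrary large coefficient with a standard error in the thousands. A committee given that output would have neither an effect size nor a usable interval, and, if the default Wald test is printed, a p-value near 1 whatever the count in the other arm.

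**Working it through.** **Inputs.** From the article: 30 per arm and 60 in total ({14}); 1:1 allocation ({16a}); severe-sepsis mortality of 28.3% to 41% (Background and rationale {6a}). Assumed: a control rate of 2% to 5% for an uncommon adverse event type, since the article gives no adverse event rate; and 15 per arm at the look, since the trigger does not fix a number of patients.

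**The plan's own figure.** The sample size rests on CRP: 2 × (1.96 + 0.84)² × 37² / 30² = 23.85, so 24 per arm; 24 / (1 − 0.20) = 30 with an implied 20% drop-out. It reproduces. No figure for safety is given.

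**Chance of an empty control arm**, (1 − p)ⁿ:

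| Control rate (assumed) | n = 15 | n = 30 |
|---|---|---|
| 2% | 0.98¹⁵ = 0.74 | 0.98³⁰ = 0.55 |
| 5% | 0.95¹⁵ = 0.46 | 0.95³⁰ = 0.21 |

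**One-arm events, 6/30 against 0/30.**

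- Odds ratio: (6 × 30) / (24 × 0), not finite. An unpenalised fit stopped at a coefficient of 19.8 with standard error 7338 (Wald p = 0.998); another stopped at 22.2 with standard error 14508 (p = 0.999). Both numbers reflect only where the iterations ended.
- Fisher's exact test: the probability that all 6 events fall in one given arm is C(30,6)/C(60,6) = 0.0119; two-sided p = 2 × 0.0119 = 0.024.
- Mid-p (doubled one-sided form): 2 × ½ × 0.0119 = 0.012.
- Likelihood ratio: log-likelihood −15.012 with separate rates and −19.505 with a common rate; 2 × 4.493 = 8.99 on 1 degree of freedom, p = 0.003.

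The Wald p does not respond to the count: 10/30 against 0/30 still gives 0.998, where Fisher gives 0.0008. With 15 per arm, 6 against 0 gives Wald 0.998, Fisher 0.017 and likelihood ratio 0.002.

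**What an interval would show for 6/30 against 0/30.** The Wilson limits are 0.095 to 0.373 for 6/30 and 0 to 0.1135 for 0/30. Combined as a score-based (Newcombe) interval for the difference of 0.20: lower 0.20 − √(0.105² + 0.1135²) = 0.045, upper 0.20 + (0.373 − 0.20) = 0.373. The committee would see an excess of 20 percentage points, from about 5 to 37.

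**Error rate of the likelihood-ratio test.** Summing the two-binomial probabilities over all tables with p < 0.05, at a true rate of 5% in both arms and 30 per arm, gives 0.083 against a nominal 0.05. This depends on the rate: at 2% the same sum gives 0.024.

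**Deaths.** 60 × 0.283 = 17 and 60 × 0.41 = 25 deaths. The chance of no deaths in an arm of 15 at 28.3% is 0.717¹⁵ = 0.007, so an empty arm is not expected there.

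**The case against.** The article names a model, not a Wald test. The likelihood-ratio test of that same model is small in the example above, and the choice of test could sit in an analysis plan that is not shown. This stands, and it is why the point cannot be that the planned analysis will return a p-value near 1. What remains is that the likelihood-ratio test leaves the odds ratio infinite, so there is still no estimate to report, and that it can reject too often. The model itself is already fixed in {21b}, so revising it corrects stated text and does not ask for missing detail.

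A reader might infer that logistic regression is to blame for missing most relevant harms. The documents do not support this. Low power comes from 60 patients: for an assumed 28% against 48%, Fisher's test has less power than Wald (0.10 against 0.16 with 15 per arm, 0.26 against 0.35 with 30). An 80% chance of detecting 5% against 20% would need 76 per arm with any standard comparison of proportions.

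A reader might also infer a rule that p > 0.05 means safe. No such rule is written: the 0.05 level stands under the efficacy outcomes, {21b} leaves the results to the committee's evaluation, and individual events are reported separately under {11b} and {22}.

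Finally, few expected events is an inference from the wording of {22}, not a stated figure. It may not hold for diarrhea and does not hold for deaths.

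**Conclusion.** The concern holds in a limited form and is minor. For uncommon adverse event types confined to one arm, the ordinary fit of the named model yields no usable odds ratio, Wald interval or Wald p-value, and a better presentation is available at almost no cost. The chance of meeting an empty control arm is 46% to 74% with 15 per arm and 21% to 55% with 30, on assumed control rates of 2% to 5% and an assumed half-way look; at a 10% rate it falls to 21% and 4%. The point also assumes that the model would be fitted to single event types, which the article does not say. It does not extend to deaths, nor to a claim that another test would make this trial able to detect harm reliably.

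**What to change.** In Interim analyses {21b}, replace the named model with wording such as: For deaths, serious adverse events and each adverse event type, we will report the number of patients with an event per arm, the risk difference with an exact or score-based 95% confidence interval, and a mid-p exact p-value; if a model is used, it will be Firth's penalised logistic regression. A non-significant result will not be taken as evidence of safety.

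This costs one or two sentences and a simpler analysis, with no extra patients, data or staff. Mid-p is preferable to the plain Fisher p-value, which is conservative at these sizes. The downside is that the wide intervals will show openly that 60 patients cannot rule out a relevant excess of harm. The change does not raise the power in any material way.
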